## Abstract

**Background:**

The X:IT intervention, conducted in 2010 to 2013, showed overall smoking preventive effect. However, parts of the intervention appeared less appealing to children from families with lower socioeconomic backgrounds. Therefore, the intervention components were modified and an evaluation of the amended intervention X:IT II is needed to show the effect of this revised intervention and whether children from different social backgrounds benefits equally from the current intervention.

**Methods:**

Main intervention components are smoke free schools, a curricular component, and parental involvement (smoke free agreements and talks about tobacco). Components have been revised from the first version; 1) previously, schools should be smoke free on the school ground and were encouraged to hide smoking so that it wasn’t visible to pupils from the school ground. Now they are encouraged to tighten the rules so that no pupils or teachers smoke during the school day, no matter where they are; 2) the specifically developed educational material (Up in Smoke) has been revised so that all materials are online and all texts has a ARI; 3) the parental involvement is now targeted multiple groups of parents, e.g. parents that are smokers, and parents of children that smoke. Language used is simpler and the website for parents presents very specific examples.

X:IT is implemented in 46 Danish public schools from fall 2017 until summer 2020. Data is collected through electronic questionnaires to students and coordinators four times (fall 2017, spring/summer 2018, 2019 and 2020). Further, qualitative interviews and observations are conducted.

**Discussion:**

Prevalence of smoking among Danish adolescents is high compared to other Nordic countries and there is social inequality in smoking, leaving individuals from the lowest social backgrounds at higher risk. Although there has been an overall decline in smoking among Danish adolescents over the last decades, a recent levelling of this development indicates an urgent need for smoking prevention in Denmark. The X:IT intervention has the potential to prevent uptake of smoking among adolescents. However, there is a particular need for evaluating the effectiveness of the revised X:IT intervention, X:IT II, with focus on the effect across socioeconomic groups of adolescents.

**Trial registration:**

Current Controlled Trials ISRCTN31292019, date of registration 24/10/2017. Retrospectively registered.

## Background

In Denmark, as well as in most Westernized countries, smoking is more prevalent among adolescents from lower socioeconomic positions (SEP) [1]. While 8 % of 15-year old Danish adolescents from higher SEP smoke (daily or less), up to 24% of adolescents whose parents receive welfare benefits are smokers [2]. Furthermore, adolescents from low SEP seem less likely to quit smoking in adulthood [3]. Public health interventions to reduce risk behaviours (e.g. smoking) should aim at being equally effective across socioeconomic groups or at being more effective among individuals from low SEP [4].

Interventions addressing health and health behaviours in childhood or adolescence have the potential to prevent or decrease socioeconomic inequalities in health behaviours later in life [5]. On the other hand, interventions themselves may generate or increase socioeconomic inequalities in health behaviours, e.g. in smoking [6]. This is problematic to the extent that interventions may be less effective or have counter-effects in the most at risk groups, often low SEP. Socially differential effects of interventions may arise at a number of points in the implementation process of an intervention, including intervention efficacy, service provision or access to materials and tools, uptake, and compliance [7]. Most intervention studies on smoking have not addressed these aspects and therefore, the mechanisms behind any inequality or lack of inequality of the effect of interventions are unknown. It has been argued that interventions targeting individual aspects related to behavioral change are more likely to widen social inequalities compared to interventions targeting the environment, because the interventions targeting the individual directly require more effort and resources from each individual [8].

Schools are regarded suitable settings for prevention activities for children and adolescents, as the school setting offers the possibility to reach almost all within the relevant age group and across different socioeconomic positions [9, 10]. In the past decades, a large number of school-based smoking prevention programs have been implemented internationally, but evaluations have shown contrasting results regarding their effectiveness [11]. Generally, strategies using comprehensive components, including environmental strategies, have been found more effective than exclusively information based interventions, which have shown limited or no effect [12, 13]. The history of school based smoking prevention in Denmark includes participation in the international intervention study “The European Smoking Prevention Framework Approach” (ESFA). Unfortunately, there was no effect of ESFA in Denmark [14]. Two other school-based interventions in Denmark, “Smoke-free classes” and “Tackling” also reported no effect [15, 16].

In 2010, the Danish Cancer Society launched the X:IT intervention. The effect of the intervention was tested in a randomized controlled trial, testing the implementation in 53 Danish schools compared to 41 control schools from 2010 to 2013 [17]. X:IT turned out to reduce smoking uptake with up to 25% among participants after the first year of study [18]. However, the qualitative process evaluation showed that some of the intervention components were less appealing to children from lower socioeconomic positions [19], indicating that X:IT in the first version might have limited appeal to the group of adolescents from lower SEP. Therefore, the intervention components have been modified and an evaluation of this revised intervention X:IT II is needed to show whether pupils from different social backgrounds benefits equally from the intervention. This paper presents the modified X:IT II intervention and its intervention components as well as the design of the effect and process evaluation of X:IT II.

### The X:IT trial

The first X:IT study was a large-scale cluster randomized controlled trial conducted in 94 schools testing the effectiveness of the X:IT intervention among 13- to 15-year-olds [17].

The intervention was developed and implemented by the Danish Cancer Society. The Centre for Intervention Research was responsible for thorough scientific evaluation of implementation and effect of the intervention [18–21]. The X:IT intervention was developed using the Intervention Mapping Protocol as a systematic planning tool [22] and the Theory of Triadic Influences as theoretical framework [23].

The X:IT intervention targeted all students attending grade 7 to 9 (13- to 15-year-olds) in the intervention schools and X:IT included three main intervention components:smoke free school groundsparental involvement comprising two dimensions – (a) smoke free contract between the student and an adult person, preferably a parent, (b) smoke free dialogues between student and parents/adultsa smoke free curriculum based on self-efficacy training and appraisal of outcome expectancies

The intervention was implemented from autumn 2010 until spring 2013 [17]. The effect evaluation showed the intervention to be effective in achieving its pre-specified aim of reducing smoking by 25% after the first year of intervention; the odds ratio for smoking among students attending an intervention school compared to control schools was 0.61 (95% CI: 0.45–0.82) [18]. Unfortunately, we saw a decrease in implementation over time; hence we were unable to show any effect after the second year [24]. Thorough examinations of the implementation process showed the importance of the degree of implementation for the intervention effects. Compared to students who were not exposed to the intervention, these analyses showed a stepwise increase in the effect of the intervention from OR 0.65 (CI: 0.43–0.97) for uptake of smoking for students exposed to medium implementation to OR 0.44 (CI: 0.32–0.68) for students exposed to full implementation of the intervention after the first year. Low implementation of the intervention did not significantly influence the smoking uptake among adolescents [20]. Further, subgroup analyses showed the importance of sufficient implementation of each of the three main intervention components [25].

As part of a thorough process evaluation of the X:IT intervention, a qualitative study among parents and children from low socioeconomic backgrounds participating in the X:IT intervention was conducted by The Danish Cancer Society [19]. The evaluation pointed at some important flaws in the applicability of the X:IT intervention for this group of adolescents and parents. The evaluation suggested that parents from low social class perceived the language used in the parental component as too academic. Parents who smoked wished for practical guides showing how to back up their children to stay smoke free [19]. Also, the educational material used in the X:IT intervention was criticized for using language which was challenging for many children from low social class background, as they are facing a risk of reading or literacy difficulties. Hence, there was a need to improve the X:IT components and test the reach and effect of a revised intervention among adolescents and parents from low social background before recommending national scale-up of the intervention.

## Methods and design

### Setting

Denmark has 98 municipalities with an average 55,000 inhabitants. There is approximately one school per 5000 inhabitants in a municipality. The Danish public school consists of grade 0 (preschool class) and grade 1–9. All 10 years are mandatory education. Danish children start school the year they turn 6. Children who start together in the same class at grade 0 will often belong to the same class/group of children through all ten years of schooling. In Denmark, children are not postponed or moved forward educationally due to academic skills or achievements, as is the case in many other countries. There is a limit of 28 children per class. Schools with grade 7–9 students usually have 2–4 parallel tracks. There is no grouping by ability in the Danish schools i.e. all children have joint lecturing. Among Danish children 85% attend public schools. The schools’ catchment area almost always comprises a wide distribution of socioeconomic background circumstances of students.

Parents have an important position at Danish schools. All schools are headed by a School Board, which is the highest deciding body at the school. The School Board has 5–7 parent representatives, two pupil members, and two staff members. The principal does not have a voting position, but is secretariat for the Board. All parents may be elected members of the School Board.

### The evaluation of X:IT II

The X:IT II intervention consists of the same three main intervention components, however in a revised form as described in the following.

#### Intervention components

##### Smoke free school grounds (smoke free school time)

Compared to most countries in the Western world, Denmark has had a very lenient smoking policy. Cigarette prices are relatively low and the first law restricting smoking in public places was adopted in 2007. In August 2012 smoking was fully banned for students, employees and visitors at Danish school grounds. This law was passed during the period of the first evaluation of X:IT. Therefore, the smoke free school ground component was revised accordingly. In the X:IT II intervention, the rules for smoke free schools are even firmer than the national law; here schools are encouraged to secure that there is no smoking anywhere at the school ground, or outside the school ground, during school hours. In Denmark, this is known as ´Smoke free school time´. The smoke free school time applies for students as well as teachers, other employees and visitors. Previous studies showed that students exposed to teacher smoking during the school day were more susceptible to smoke themselves [26–28].

##### Parental involvement

Two other Nordic studies have successfully used smoke free contracts between pupils and parents [29, 30]. In the Swedish study, the smoke free contract seemed to reduce the smoking prevalence by almost 50% among 14- to 15-year-olds [30]. Signing a smoke free contract is a manifestation of an active choice of non-smoking. When signing the contract, the pupil promises to stay smoke free for the following year. One of the parents, or another significant adult, co-signs the contract. The adult hereby commit to support the adolescent’s choice of staying smoke free and also to have a smoke free dialogue with their child. Having a smoke free dialogue involves that the adults clearly distance themselves from adolescent smoking, and asks about the child’s thoughts and experiences with tobacco.

In X:IT II, the smoke free contract and the smoke free dialogue have been revised. The material addressing parents, i.e. the homepage, leaflets, and the smoke-free contract, have been revised in order to tailor the language and information specifically for parents from lower SEP. The new material is now targeting various groups of parents: smoking parents, non-smoking parents, and parents with smoking children. The material has been revised to make the communication more unequivocal, relevant, and easier to read. For example, the material previously called ‘Smoke free dialogue’ is now called ‘Chat on tobacco’. The homepage (http://www.snakomtobak.dk/, In English: Chat on Tobacco) has become interactive and visually improved by use of videos, quizzes, dilemma games, and pictures. Further, the smoke free contract is renamed to “smoke free agreement” in order to make it more informal. As in the first version of X:IT, in X:IT II students with a signed smoke free agreement are able to win a prize [17].

The teachers present the X:IT II intervention to the parents at parent meetings at the beginning of each school year.

##### Smoke free curriculum

Generally, there is no strong evidence for the effectiveness of school-based programs that provide information-giving curricula only. However, information-giving programs seem to be effective if included in multi-model programs [13]. Programs based on social influence approaches which include: correcting adolescents’ perceptive overestimation of smoking prevalence; recognizing high-risk situations; increasing awareness of media, peer and family influences; teaching and practicing refusal skills; and making public commitments not to smoke, have been shown to be effective [13, 31].

The educational material ‘Gå op i Røg’ (Up in Smoke) is based on the knowledge above. The program has been developed to target students at grade 7 to 9 (age 13–15 years), and includes eight lessons a year for three years. It can be used in several different subjects (cross-curricular). All texts have been made available online and the automated readability index (ARI) is lowered. The general readability has been improved, i.e. a glossary appears when clicking on academic words such as ‘cancer’ and ´oxygen´. Furthermore, the educational material is now easier to differentiate according to the students´ academic level [19].

Based on the process evaluation from the first evaluation of X:IT, the homepage (http://www.op-i-roeg.dk/) has been revised to meet some of the requests from the teachers, e.g. online teaching has been made available. Further, theme packages have been developed as they may require involvement from fewer teachers, an issue which was addressed in the first evaluation. The educational component of the intervention may still be taken on by one or more teachers from each class, according to the wishes and opportunities of each school. Schools can decide whether lessons are delivered during the whole school year or in special project days.

An overview of all intervention components in the X:IT II intervention is presented in Table 1. The table shows the main intervention components and any additional intervention activities. The table contains information on timing of all the activities including learning objectives for each activity.

**Table 1 Tab1:** Intervention components of the X:IT II intervention, including timing of activities and learning objectives for each activity

	Setting	Intervention component	Timing	Aims
Main intervention components	School	Smoke free school time	Throughout the study period	- Remove exposure to smoking
				- Increase identification with non-smokers
				- Contribute to creating smoke-free environments
		Parent-teacher meetings	Start of every school term	- Present study information, especially the smoke free agreement
	Class	Smoke free curriculum	At least 8 lessons each year in year 7, 8 and 9	- Increase awareness of long- and short-term risks of smoking
				- Reduce majority misunderstanding
				- Increase awareness of smoking inducing mechanisms in society
				- Increase individual ability to resist temptation to smoke
				- Increase identification with non-smokers
				- Contribute to creating smoke-free environments
	Home/parents	Smoke free agreements and chat on tobacco	Start of every school term	- Create supportive smoke free environment at home
				- Signal opposition to adolescent smoking
				- Reduce availability of cigarettes
				- Reduce exposure to smoking
				- Increase identification with non-smokers
				- Contribute to creating smoke-free environments
Implementation and sustainability	School	Kick-off workshops for school coordinators and leaders	Before start of study, August 2017	- Inform about background and methods of the study
		Newsletters for schools	3–4 each year throughout study period	- Inform about study
				- Ensure sustainability of the study
		Study reports for each school	Fall 2018	- Inform about prevalences from study
				- Ensure sustainability of the study

### Hypotheses

Based on these modifications of the X:IT intervention, we hypothesize that:the X:IT intervention material, carefully developed to take into account the intellectual skills and academic performance of adolescents´ and their parents´, will improve the reach of the intervention among low socioeconomic background.the X:IT intervention study will have an overall effect of a 25% reduction in smoking uptake at age 13.the X:IT intervention study will reduce smoking uptake among low socioeconomic position adolescents to the same extent or more than among adolescents with a high socioeconomic position background.

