### Evaluation

#### Design

The X:IT II intervention will be evaluated by means of effect in a difference-in-difference design. Hence, all participating schools will receive the same intervention, and students from high and low social classes will be compared in the difference-in-difference design [32]. Process evaluation will be conducted at specific time points during the intervention period. Data collections are shown in Table 2.

**Table 2 Tab2:** Data collection of the X:IT II study – timeline, instrument and source of data

	Baseline September 2018	Intervention	Follow-up 1 May 2018	Intervention	Follow-up 2 April 2019	Intervention	Follow-up 3 April 2020
Students	Questionnaires (students start year 7)		Questionnaires (students end year 7)	Observations and interviews	Questionnaires (students end year 8)		Questionnaires (students end year 9)
School coordinators	Questionnaires		Questionnaires		Questionnaires		Questionnaires
Teachers		Monthly questionnaires on curricular activities (September – June)		Observations and interviews Monthly questionnaires on curricular activities (September – June)		Monthly questionnaires on curricular activities (September – June)	

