#### Recruitment plan and study population

The recruitment period ran from January 2017 till June 2017, the intervention started in September 2017 and runs until June 2020. The recruitment ended up having two steps. First, 300 schools were randomly selected and contacted by email and by postal letter, followed up by telephone calls. The aim of this first step was to recruit 156 schools, which could be randomly selected into an intervention and a control group, i.e. to conduct a randomized controlled trial.

However, after contacting each of the 300 schools by telephone, it became clear that this aim was too ambitious, as only 60 schools showed any interest to be included in the study. In the second step of the recruitment phase, we decided to include all interested schools as intervention schools. However, three of these schools were for children with special needs and were therefore excluded from the evaluation, leaving 57 schools. After the summer holiday, when the final commitment from schools were needed and the data collection was about to start, 11 of the schools withdrew from the evaluation; in two schools, there was a new school leader who did not prioritize the intervention; two schools had assigned to too many projects and had to prioritize; at the remaining seven schools lack of time was the primary reason for resigning. Therefore, baseline data included 46 schools from all over Denmark.

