#### Power calculations

Power calculations were based on the following assumptions: Each school cluster includes on average 50 students, the intra class coefficient for current smoking among grade 9 students is 0.053, smoking prevalence of 17.9% in grade 9, an expected reduction in smoking of 25 to 13.4%, and a power of 80%. Power calculations were conducted according to Donner & Klar (1996) [33] and showed a need for 48 schools with approximately 2400 students.

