### Statistical methods

#### Data process and analyses

The analyses of effect will be based on the principles of the difference-in-difference approach. The difference-in-difference design compares outcomes after and before an intervention between an exposure group and a comparison group [32]. In the evaluation of X:IT II, we will consider the group of students with high SEP as the comparison group (group C) and students with low SEP as the exposed group (group E). This means that the change in outcomes can be estimated as (Cafter-Cbefore) - (Eafter-Ebefore). If X:IT II works equally well for students from both high and low SEP, the difference-in-difference estimate is equal to 0 which is the aim of X:IT II.

The difference-in-difference estimates will be conducted in regression models rather than by simple subtraction which allows adjusting for confounders. We will conduct both per-protocol analyses and intention-to-treat (ITT) analyses using multiple imputation of missing values. Furthermore, we will use statistical methods that take into account the multilevel structure of the design of the study.

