To further improve the evidence from this study, a thorough process evaluation is planned including both qualitative and quantitative methods. The qualitative evaluation will seek to understand how teachers work with the intervention and under which circumstances the best implementation is obtained. Further, we will obtain knowledge and understanding on how students perceive and receive the intervention. The quantitative process evaluation will, as was the case in the former evaluation of X:IT, be based on students receiving the intervention. Also, school capacity to implement, as well as the actual obtained implementation, will be assessed. Like in the X:IT study [20, 25], we will conduct analyses taking the actual implementation into account in the effect evaluation. Hereby, we will be able to draw conclusions about the effectiveness of the X:IT evaluation. We will examine intervention effects in relation to the actual implementation at the school as well as the individual level. Numbers of students receiving the intervention in X:IT II is almost equal to the group of intervention pupils from the first evaluation. Analyses will therefore be comparable to each other.

If shown to be effective, the X:IT II study will provide important information on how to prevent smoking uptake effectively also among the group of adolescents from low socioeconomic backgrounds who are currently at higher risk of smoking uptake in Denmark.

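### Hypothesis 2 claims an overall 25% reduction in smoking uptake, but the design as fixed contains no untreated reference against which a reduction could be estimated

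*Protocol article*

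**What the plan says.** All references are to the protocol article.

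- **Hypotheses:** the second of three hypotheses is that "the X:IT intervention study will have an overall effect of a 25% reduction in smoking uptake at age 13". The third, on equal or greater benefit in low SEP, is separate.
- **Recruitment plan and study population:** a randomised trial was the first aim. When too few schools showed interest, "we decided to include all interested schools as intervention schools".
- **Design:** "all participating schools will receive the same intervention, and students from high and low social classes will be compared in the difference-in-difference design".
- **Data process and analyses:** "we will consider the group of students with high SEP as the comparison group (group C) and students with low SEP as the exposed group". The estimate is the before-after change in high SEP minus the change in low SEP, and "If X:IT II works equally well for students from both high and low SEP, the difference-in-difference estimate is equal to 0", which is declared to be the aim.
- **Discussion:** the main purpose is given as the difference between high and low SEP. Effects will also be examined by degree of implementation at school and student level, and the article continues: "Hereby, we will be able to draw conclusions about the effectiveness of the X:IT evaluation". The closing paragraph is conditional on the programme being shown to be effective.

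No section names an untreated, external or historical group as the reference for hypothesis 2.

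**The concern.** An overall reduction in uptake is a statement about what would have happened in these schools without X:IT II. Once the control schools were given up, nothing observed in the study carries that information. The SEP contrast asks whether two treated groups changed by different amounts, which is hypothesis 3.

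X:IT II could have no effect in either group without the planned analysis revealing it. This is a realistic possibility: the section on the first trial reports no demonstrable effect after the second year and no significant influence of low implementation. The Background presents testing of the revised programme as a step before recommending national scale-up, so an effectiveness claim without a counterfactual could carry weight.

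**Working it through.** **Inputs**

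- 25% overall reduction (Hypotheses).
- 17.9% smoking in grade 9, expected to fall to 13.4% (Power calculations). Check: 0.179 x 0.75 = 0.134, so this is the same 25%.
- 8% smoking among 15-year-olds of higher SEP, and up to 24% where parents receive welfare benefits (Background). These are used only as illustrative untreated rates; the 24% is an upper figure for a particular group, not a low-SEP average.
- Very few smokers at the start of grade 7 (Discussion). A baseline of 0 is assumed below.

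**What the estimate contains**

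For high SEP (C) and low SEP (E), let b be baseline smoking, u the follow-up level without the programme, and d the programme's effect. Observed follow-up is u + d. Then

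DiD = (uC + dC - bC) - (uE + dE - bE) = [(uC - bC) - (uE - bE)] + (dC - dE).

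The first bracket is the SEP gap in untreated growth. Hypothesis 2 concerns the size of d relative to u. The study observes u + d and never u alone.

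**Numbers (baseline 0, so DiD is the follow-up difference)**

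| Scenario | High SEP | Low SEP | DiD, points |
|---|---|---|---|
| No effect, untreated 8% and 24% | 8 | 24 | -16 |
| Common 2-point reduction from 8% and 24% | 6 | 22 | -16 |
| Common 25% relative reduction from 8% and 24% | 6 | 18 | -12 |
| No effect, untreated 8% and 20% (assumed) | 8 | 20 | -12 |
| No effect, untreated 17.9% in both (assumed) | 17.9 | 17.9 | 0 |
| 25% reduction from 17.9% in both (assumed) | 13.4 | 13.4 | 0 |

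- Rows 1 and 2: a common absolute effect cancels exactly.
- Rows 3 and 4: a common relative effect does move the additive estimate, but the same value arises with no effect and a smaller untreated gap. That gap is unknown.
- Rows 5 and 6: the target value of 0 is reached with no effect and with the full hypothesised effect.
- On a ratio scale a common relative effect cancels: 8/24 = 6/18 = 4/12 = 1/3 (log ratio -1.10) for reductions of 0%, 25% and 50%.

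**Before-after change**

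From a baseline near zero, the plan's own grade 9 figures imply a rise of about 17.9 points without an effect and about 13.4 points with one. Both are increases. Telling them apart requires knowing the untreated level in these schools in these years; 17.9% is a planning assumption, not an observation from them. The article gives no untreated rate for age 13, the age named in hypothesis 2.

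**Implementation analyses**

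These compare treated schools and students with each other. The first trial's analysis of this kind used students not exposed to the intervention as reference. X:IT II as designed has no such students, and degree of implementation is not randomised.

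**The case against.** Several points on the other side have force, and some stronger readings that a reader might infer do not hold.

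- *That the SEP contrast is the only planned analysis.* It is not. Degree of implementation is a primary outcome, and the Discussion rests its effectiveness sentence on the implementation analyses. They still cannot supply an overall 25% effect, because they are non-randomised and have no specified unexposed reference.
- *That the difference-in-difference is blind to every common effect.* This is true on the additive scale for an absolute effect only. A common 25% relative reduction shifts the example from -16 to -12 points. The shift cannot be read as an effect, because the untreated gap is not known.
- *That the randomised trial's power calculation was simply kept.* The Discussion gives 78 plus 78 schools for the randomised design and presents 48 as a calculation for the difference-in-difference design. The present point does not depend on that figure.
- *That hypothesis 1, on reach, also lacks a reference.* Its reference is evidently the first version of X:IT. How that comparison is analysed may properly be left to a fuller document.
- *That the limitation is already disclosed.* In part: the Discussion concedes the lost randomisation and makes the SEP difference the main purpose. It does not withdraw or qualify hypothesis 2.
- *That the Discussion promises comparability with the first evaluation.* That statement rests on similar numbers of students receiving the intervention; it names no comparison with the first trial's control schools.
- *That an analysis plan may settle it.* No analysis plan can create concurrent control schools. A historical comparison could be specified elsewhere, but the article describes the effect analysis as the SEP contrast.

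**Conclusion.** The point stands as a contradiction between hypothesis 2 and the design as fixed. One of three stated hypotheses has no counterfactual, and neither the difference-in-difference, nor before-after change, nor the implementation analyses can provide one. In the illustration, identical estimates (-16, -12 or 0 points) arise with and without a programme effect.

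The algebra needs no numerical assumption. The table assumes a zero baseline and illustrative untreated rates; other rates change the values, not the conclusion. Hypothesis 3 is a separate question, and the SEP comparison can remain. The text is wrong as written and affects what the study may conclude, so it should be corrected before results are reported against hypothesis 2.

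**What to change.** 1. Withdraw hypothesis 2, or restate it as descriptive: smoking prevalence at the end of grades 7, 8 and 9 under X:IT II, overall and by SEP, with intervals that allow for clustering by school.
2. In the Discussion, limit the effectiveness wording, including the closing conditional sentence, to differences by SEP and associations with degree of implementation under X:IT II.
3. Next to the target value of 0, state that it does not distinguish an equal effect from no effect.
4. Optionally, if comparable control-school data from the first trial exist with the same smoking item (the article does not show that they do), add a comparison with them as a secondary, explicitly non-randomised historical analysis. State as limits the decline in adolescent smoking over recent decades (Abstract) and the August 2012 ban on school grounds, which took effect during the first trial. Either could produce an apparent reduction without any programme effect.

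Items 1 to 3 cost wording only. The downside is that the study gives up an overall-effect claim, which its design cannot support. Item 4 costs data access and one further analysis.
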